#### Post-intervention

Saliva samples will be collected by the hypnotherapist 10 minutes following dressing changes. Information will be recorded regarding children’s medications, time of last waking up, the last brushing of teeth, food/drink/gum intake during the previous hour, and caffeine consumption during the collection day. The date and time of collection and the volume of saliva samples will be recorded. Samples will be stored at 4°C to be spun in a centrifuge at 1400 × *g* for 10 min at room temperature and then frozen at −80°C until analysis in triplicate within 7 days. Following the collection of data on sociodemographic characteristics and process evaluation outcomes, data analysis, and synthesis will be performed.

### Study timeline

The study will commence in March 2022 and is expected to be conducted over 15 weeks as shown in the flow diagram (Fig. 1). Enrolment will remain open until July 2022.

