**Methods:**

An observational mixed-methods feasibility and acceptability study will be conducted over 15 weeks. Eligible children (*N* = 30) aged 4 to 16 years presenting to a paediatric burns outpatient centre in a metropolitan children’s hospital in Australia with acute burns requiring dressing changes will be included. Eligible parents of children (*N* = up to 30) and clinicians who perform dressing changes (*N* = up to 20) will also be included. Child participants screened as having medium to high suggestibility as assessed by behavioural measures will receive hypnotherapy during dressing changes. A process evaluation will target feasibility and acceptability as primary outcomes and implementation (i.e. fidelity in delivery), reach, potential effectiveness, and adoption of evaluation procedures and intervention as secondary outcomes.

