#### Sample size

A formal sample size calculation is not required for feasibility studies [32]. Hypnotherapy will be conducted with 30 children over 15 weeks. The sample size is estimated based on clinic data in the study setting indicating that at least five potentially eligible children present with acute burns each week. Considering a non-participation rate of 15% of the potentially eligible children and the exclusion of 15% of children with low hypnotic suggestibility, it is estimated that 15 weeks will be required to recruit at least 30 eligible children. This number of participants is estimated to be adequate to generate enough information on the feasibility and acceptability of the intervention and study procedures. Participants will be followed up for approximately 5 weeks as the average number of dressing changes is five (one dressing change per week). The participation rate and recruitment time will inform sample size calculations in future studies.

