#### Hypnotherapeutic session

Hypnotherapeutic sessions consist of induction, deepening (i.e. intensification) techniques, and therapeutic suggestions prior to counter-suggestions (Table 3). A maximum of five sessions will be provided during dressing changes that are usually performed every 3 days or weekly. Sessions will thus have the same duration as the burns dressing change, which is usually between 20 and 35 minutes. During the first dressing change, the session will be reduced to therapeutic suggestions following the standard induction included in the hypnotic suggestibility scale. Pre-recorded music will accompany sessions (supplementary file 2- table B) [8, 42]. External distractions will be minimised as much as possible with the hypnotherapist being the only person talking to the child whenever possible. Following clinical policies and to reduce separation anxiety, parents will be encouraged to be present during sessions, unless they choose not to do so [15].

**Table 3 Tab3:** Description of the phases and components of the hypnotherapeutic session

Phase	Core components	Description of components	Goal
Induction	Positioning	Ask children to be in a comfortable position for hypnosis [8].	To promote comfort and relaxation [8].
	Eye fixation and abbreviated progressive muscle relaxation	Ask children to focus their attention on the hypnotherapist’s hand while tensing their hand’s muscles for a few seconds before releasing tensions [8].	To elicit relaxation, shift of attention, absorption in hypnosis, and dissociation from the painful stimulus [43, 44].
	Eye closure	Ask children to optionally close their eyes [8].	To block external distractions and promote internal absorption [37].
	Lifting of the hand	Ask children to keep their hands in a vertical position.^a^	To promote numbness in the hand and response expectancies during glove anaesthesia.
	Deliberate faster breathwork and suggestions for relaxation	Ask children to maintain faster and deeper rhythmic breathing for a few minutes then to gradually relax body muscles following pleasant imagery suggestions (e.g. *blowing tensions away and inhaling relaxing lights*) [8].	To enhance suggestibility by inducing mental and physical relaxation; promote positive coping by distraction; establish the hypnotic context; and promote response expectancies [8, 43, 44].

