### Procedures

#### Recruitment

Children presenting to the specialist burns centre for their first burns dressing change and their parents will be screened for eligibility after consulting with clinicians regarding children’s potential eligibility. It is anticipated that approximately three children per week will be recruited (total recruitment period 15 weeks).

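### The same 15 weeks is given to recruitment alone and to the whole study, although each child is followed for about 5 weeks; the recruitment figure also does not follow from the stated rates

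*Protocol article*

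**What the plan says.** Five places in the protocol article bear on duration.

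- **Abstract, Methods:** "An observational mixed-methods feasibility and acceptability study will be conducted over 15 weeks".
- **Study timeline:** "The study will commence in March 2022 and is expected to be conducted over 15 weeks", with the detail referred to Fig. 1, and then "Enrolment will remain open until July 2022".
- **Sample size:** "it is estimated that 15 weeks will be required to recruit at least 30 eligible children". The inputs are at least five potentially eligible children per week, 15% non-participation and 15% excluded for low suggestibility. The section then states "Participants will be followed up for approximately 5 weeks as the average number of dressing changes is five (one dressing change per week".
- **Recruitment:** "It is anticipated that approximately three children per week will be recruited (total recruitment period 15 weeks".
- **Hypnotherapeutic session:** at most five sessions, given at "dressing changes that are usually performed every 3 days or weekly".

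Progression criteria requires study completion above 50% and collection of more than 50% of data across all time points. Tables 5 and 6 place retention at each dressing change, itch ratings from the third change onward, and the closing interview at the last change.

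**The concern.** A study that enrols for 15 weeks and then follows its last child for about 5 weeks does not last 15 weeks. Either the total duration is understated or the recruitment period is overstated, and the text does not let a reader tell which.

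This matters because time is itself a result here. Sample size says that recruitment time and the participation rate will inform later sample size calculations. Completion, retention and data completeness are feasibility outcomes and feed the progression criteria. If the site treated week 15 as the end of data collection while still enrolling, some late entrants would lose sessions for a calendar reason. Those losses would be mixed with drop-out caused by burden or refusal.

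**Working it through.** **1. The plan's own figure: 15 weeks to recruit 30 children.** Weeks needed = 30 / weekly rate.

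| Weekly rate | Source | Weeks to reach 30 | Children in 15 weeks |
|---|---|---|---|
| 5 × 0.85 × 0.85 = 3.61 | Sample size, losses applied in sequence | 8.3 | 54.2 |
| 5 × (1 − 0.30) = 3.5 | Sample size, losses added | 8.6 | 52.5 |
| 3 | Recruitment | 10.0 | 45 |
| 2 | not stated anywhere | 15.0 | 30 |

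The 15 weeks is not reproduced by any stated rate. Only 2 per week gives it. If the 3 per week counted children before the suggestibility exclusion, which the text does not say, the rate would be 3 × 0.85 = 2.55 and the time 30 / 2.55 = 11.8 weeks, still not 15.

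**2. Total duration.** Five weekly changes span 4 weeks from first to fifth; the stated follow-up is about 5 weeks.

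- Entry to week 15: 15 + 4 = 19 weeks, or 15 + 5 = 20 weeks.
- Enrolment closed at 30 children, at the stated rates: 8.3 + 5 = 13.3 weeks to 10 + 5 = 15 weeks.

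So 15 weeks works as a total if enrolment closes at 30 at the stated rates. It does not work as a total if it is also the recruitment period.

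**3. Calendar.** A start on 1 March 2022 puts the end of week 15 on 14 June; a start on 31 March puts it on 14 July. A start on 18 March puts it on 1 July. If enrolment closes on 1 July, it outlasts week 15 only for starts before 18 March. If it closes on 31 July, it outlasts week 15 for every March start. The text fixes neither day.

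**4. Size of truncation, if it occurred.** Assumptions, none of which the text states: data collection stops at week 15, entry is even to week 15 (2 per week for 30 children), and every child has five changes.

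- *Weekly changes.* Sessions available = min(5, 16 − entry week). Entry in weeks 12, 13, 14 and 15 leaves 4, 3, 2 and 1 sessions. Children cut short: 4 × 2 = 8 of 30 (27%). Sessions lost: (1 + 2 + 3 + 4) × 2 = 20 of 150 (13%).
- *Full 5 weeks of follow-up.* 5/15 = 33%, or 10 of 30.
- *Changes every 3 days.* Four intervals × 3 = 12 days; 12/105 = 11%, or 3 to 4 of 30.

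With even entry the percentages do not depend on the rate: at 3 per week for 15 weeks it would be 12 of 45, again 27%.

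The completion ceiling before any withdrawal would be 67-73% with weekly changes and 89% with 3-day changes. About 87% of planned sessions would be delivered on the weekly schedule. Completion would fall to 50% only if retention for other reasons were 0.50/0.733 = 68% or 0.50/0.667 = 75%. Entrants in weeks 12 and 13 still reach the third dressing change, so only the 4 of 30 entering in weeks 14 and 15 would have no itch rating.

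**The case against.** The strongest reply is that nobody is cut off. The text sets no end to data collection at week 15, calls the duration expected, and gives the follow-up for participants without excepting late entrants. At the protocol's own rates, 30 children are enrolled within 10 weeks and 5 weeks of follow-up then fits. Fig. 1, which may separate enrolment from follow-up, is not available to this review. Table 5 records the amount and type of missing data, so calendar losses could be recognised.

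Most of this stands. A reader might infer that a quarter to a third of the children cannot complete, that the later outcomes are lost for all of them, or that the completion and data criteria would fail. The documents do not support that. It needs a stop at week 15 that is not written, an accrual rate of 2 per week that differs from both stated rates (for 30 children spread over 15 weeks), and five weekly changes for every child, when five is an average and a session maximum and shorter spacing is allowed. Even then both criteria are still met unless other losses are added.

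The reply does not remove the contradiction in the text. Making 15 weeks work as a total means setting aside the 15-week recruitment statements in two sections. Sample size also speaks of at least 30 children, and no rule closes enrolment at 30. A figure could show the intended timeline, but it could not make those sentences agree.

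**Conclusion.** The point holds as an inconsistency in the stated timeline. The 15 weeks cannot be both the recruitment period and the whole study when each child is followed for about 5 weeks; with entry to week 15 the total is about 19-20 weeks. The 15-week recruitment figure also disagrees with its own inputs (about 8-10 weeks for 30 children), and 3 per week for 15 weeks disagrees with the sample of 30.

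The effect on outcomes is conditional. Under the three assumptions in step 4, 27-33% of children would be cut short (about 11% with 3-day changes) and 13% of sessions lost on the weekly schedule. That would lower the completion and data rates and blur their meaning, but would not alone take either below its 50% criterion. Whether July enrolment runs past week 15 depends on the start day and on what the closing date means. The correction is worth making because it is cheap and because recruitment time and completion are among the results the study is meant to deliver.

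**What to change.** State the enrolment period and the total duration as separate figures, and make the Abstract, Sample size, Recruitment and Study timeline agree. Either of two versions would do:

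- enrolment closes at 30 children (about 10 weeks at the stated 3 per week), followed by about 5 weeks of follow-up, within 15 weeks in total; or
- enrolment runs for up to 15 weeks and data collection continues until the last child's final session and interview, about 19-20 weeks in total.

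Then:

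- align the July 2022 enrolment date with the version chosen;
- correct the recruitment estimate so that it follows from its inputs, and say at which stage of screening the 3 per week is counted;
- report any child cut off by study closure separately from drop-outs and missing data;
- reconcile the dressing-change interval between Sample size and Hypnotherapeutic session, since it sets the follow-up length.

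The first version costs wording and an enrolment rule. The second costs wording and about 4-5 more weeks of hypnotherapist time at a falling workload. Neither needs extra children beyond the planned 30.

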**Fig. 1 Fig1:**
[figure not shown]
Flow diagram describing the timeline of study procedures

#### Progression criteria

To proceed with investigating the efficacy of hypnotherapy in children with burns, at least the following criteria should be met: sufficient time to deliver the intervention in > 80% of children who commence hypnotherapy; > 50% of families with moderate to high satisfaction rate; recruitment and study completion rates > 50%; collection of > 50% of data across all time points; hypnotherapist adherence to > 50% of intervention elements in the fidelity checklist with > 50% of children; and the absence of serious side effects. The progression criteria cover components of all of the implementation outcomes (Data Synthesis, page 19, above).

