### Design

The study will be conducted using an observational mixed-methods design integrating multiple data sources (clinicians, parents, and children) and data collection methods (quantitative and qualitative) [26]. The use of different perspectives and methods is intended to avoid biases generated by relying on one source of evidence or type of data (e.g. quantitative or qualitative alone). The key outcomes are acceptability (i.e. the extent to which procedures are perceived as fit, satisfying, and appealing, based on experienced affective and cognitive reactions) [27], implementation (i.e. fidelity or the extent to which procedures are delivered as intended), and feasibility (i.e. the extent to which procedures are successfully delivered in a distinctive context that is not fully controlled) [28]. The Theoretical Framework of Acceptability (TFA) [27], Outcomes for Implementation Research [28], and the Reach, Effectiveness, Adoption, Implementation and Maintenance (RE-AIM) framework were used to guide the process evaluation [29–31] (Table 1).

**Table 1 Tab1:** Evaluation frameworks guiding the process evaluation and data collection

Evaluation framework	Implementation outcome	Definition		Data collection	
				Source	Type
RE-AIM [30, 31]	Reach^a^	Willingness of eligible families to participate in the study		Report on the rate of approached eligible families who consent to participate	Quantitative
	Effectiveness	Extent to which the intervention eliciting intended effects and the overall perceived benefits and potential undesired effects		Numeric ratings of pain, anxiety, and itch; physiologic measures of distress; data on wound re-epithelialisation	Quantitative
				Reported adverse events	Qualitative
				Reported perceived benefits	Qualitative
	Adoption by clinicians^b^	Willingness of clinicians to take part in the study		Report on the rate of clinicians conducting dressing changes who consent to join the study	Quantitative
	Implementation	The quality of delivery and consistent delivery of study procedures as intended or prescribed in the protocol (i.e. fidelity)		Report on retention rates among children	Quantitative
				Level of adherence to the fidelity checklist in delivering the intervention	Quantitative
				Completeness of collected data on health outcomes	Quantitative
				Additional adaptations and modifications	Qualitative

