### Participants

Children presenting to the study setting with acute burns requiring dressing changes, who agree with their parents to be contacted for research, will be recruited after reviewing their medical files and assessing their eligibility as advised by clinicians. Eligible children will be included with their parents and clinicians if they agree to participate. Children’s participation involves providing data and engaging in the intervention. Parents’ participation involves providing proxy-completed outcome data for children under 8 years and acceptability data. Clinicians’ participation involves rating their satisfaction with hypnotherapeutic sessions, reporting adverse events, and advising researchers on eligible families who agree to be contacted for research.

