#### Process evaluation

Outcomes of the implementation process are outlined in Table 5. Potential effectiveness will be measured by health-related outcomes of procedural pain, state anxiety, and itch at different time points as guided by the RE-AIM outcome of *effectiveness* (Table 6). The selection of health outcomes measurement tools is based on psychometric properties, feasibility, and clinical utility for children aged from 4 to 16 years (supplementary file 3). Salivary α-amylase, a bio-indicator of the sympathetic adreno-medullary system (produced by norepinephrine-responsive salivary gland cells), will be measured as a stress biomarker. The choice of salivary α-amylase was made as the authors are experienced in administering the test rapidly in children research studies, and based on the measures’ reliability, validity, and sensitivity as a marker of distress and minor stressors [50].

**Table 5 Tab5:** Process evaluation with data collection time-points

Implementation outcome	Measurement	Dressing change time point			Source of data (measurement tool)	Assessor	Dressing change
		Pre	Mid	Post			
Reach	Rate of families willing to participate out of those approached for participation	x			Report	Hypnotherapist	1st dressing change
Acceptability	Parents’ and children’s beliefs/views on hypnotherapy	x			Field notes, semi-structured pre-hypnosis interview^a^		
	Children’s level of perceived self-efficacy	x			1–10 Likert scale		
	Children’s level of positive therapy expectations	x			1–10 Likert scale		
	Satisfaction of parents and children with suggestibility screening, involuntariness measures, and pre-hypnosis interview			x	Satisfaction NRS^b^		
	Satisfaction of parents, children, and clinicians with the hypnotherapeutic session			x	Satisfaction NRS^b^		Each dressing change
	Families’ and clinicians’ likes, dislikes, recommendations, and perceived burden of required time and effort regarding hypnotherapeutic sessions			x	Semi-structured interview^a^ and field notes		Last dressing change
	Satisfaction of families with health outcomes measurements			x	Satisfaction NRS^b^		
Effectiveness	Perceived benefits			x	Field notes, reports of children, parents, and clinicians		
	Safety of hypnotherapy (rate, timing, duration, and severity of adverse events)		x	x			Each dressing change
	Health outcomes	(Refer to Table 6 for details)					

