Adoption	Rate of clinicians consenting to participate among those conducting dressing changes.	x			Report	Hypnotherapist	1st dressing change
Implementation: fidelity	Retention rate		x	x	Report on the rate of children completing the intervention		Each dressing change
	Fidelity in collecting data on health outcomes			x	Response rate in data collection forms (amount and type of missing data)		
	Fidelity in delivering the intervention			x	Study-specific checklist^c^	Independent observer expert in clinical hypnosis	
	Additional adaptations and modifications			x	Documentation of what, when, and how adaptations occurred		
Feasibility	- Adequacy of resources (adequately working music player, calm space) - Presence/absence of interruption (s) - Time availability (sufficient for delivering study procedures) [31]	x	x	x	- Field notes - Intervention pre-recording	Hypnotherapist	

^a^Following permission from children and parents to audiotape the intervention

^b^Adult participants (parents or clinicians) and children ≥ 8years will self-report their satisfaction; proxy reports will be obtained from parents for children < 8years

^c^An independent assessor (preferably hypnotherapist) will assess the fidelity of delivering the intervention through analysing pre-recordings using a study-specific checklist based on the intervention manual; % of core elements and non-core elements delivered will be reported

**Table 6 Tab6:** Health-related outcomes measured using the RE-AIM outcome of effectiveness with data collection time points

RE-AIM outcome	Health-related outcomes		Dressing change time point			Source of data (measurement tool)	Assessor	Dressing change
			Pre	Mid	Post			
Potential effectiveness	Acute procedural pain	Pain intensity	x	x retro	x	FPS-R (≤ 8 years) [51], I-INRS (≥ 8 years) [52], FLACC^a^ [53]	Hypnotherapist	Each dressing change
		Pain unpleasantness				UNRS (≥ 8 years) [52]		
	State anxiety		x	x retro	x	VAS [54]		
	Itch	Intensity			x	Itch-NRS: self-report ≥ 8 years, proxy-report < 8 years [55]		From 3rd dressing change
		Frequency				Questions on itch episodes (per week, per day) [55]		
	Physiologic measures of pain and distress	Heart rate	x	x	x	Monitoring device		Each dressing change
		Salivary α amylase (in children’s saliva samples)	x		x	ELISA kits (Stratech Scientific, Avalon NSW)	Independent observer	

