Tailoring treatment is paramount in paediatric burns given potential barriers related to the setting, clinicians, and parents as well as the unique biopsychosocial impact of burns on children’s attitude, adherence, treatment delivery, and outcomes [2, 15, 17]. Yet, pharmacological agents and distraction techniques currently used in paediatric burns lack tailoring [14, 15]. Effective tailored adjunct non-pharmacological interventions such as hypnotherapy may optimise the health care of children with burns by further reducing the already low pain reported during dressing changes and addressing state anxiety and itch, which have received less attention. Hypnotherapy can be tailored to varied settings and populations with diverse characteristics and backgrounds, which can facilitate integration into medical interventions for optimal delivery [14].

In the proposed study, hypnotherapy will be tailored to address child-related factors influencing pain and distress and keep pace with children’s changing conditions and perceptions on hypnosis, distress, and itch [8]. The intervention will be adapted to apparent child-related affective, cognitive, and sensory pain components (situational determinants) as well as symptoms of distress such as fear, discomfort, and withdrawal. Contextual and social factors of pain and distress and their interaction with internal factors will also be addressed during the intervention. For instance, the short time available to prepare children emotionally for repeated medical procedures and the duration of the hypnotic suggestibility screening (20 minutes) will make it impractical to conduct hypnotherapy following the screening. Thus, during the first dressing change, if children have a medium to high suggestibility score, the hypnotherapeutic session will be shortened to therapeutic suggestions following the standard hypnotic induction included in the hypnotic suggestibility test. Factors related to parents including misconceptions will be addressed during the pre-hypnosis interview. In addition, child-related factors that can influence hypnotic responding (e.g. attitude towards hypnosis, therapy expectations, and perceived self-efficacy) will be assessed alongside hypnotic suggestibility and addressed to promote positive outcomes [32]. However, tailoring can be challenging due to difficulties in replicating the intervention, evaluating individualised outcomes, and determining characteristics to address [61].

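### The time progression criterion cannot register children who never commence hypnotherapy because interview or screening ran out of time, and Adoption has no criterion although all outcomes are said to be covered

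*Protocol article*

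**What the plan says.** **Time.** The Progression criteria section requires "sufficient time to deliver the intervention in > 80% of children who commence hypnotherapy". Study aims and objectives and the Intervention section both define the intervention as three parts: pre-hypnosis interview, suggestibility screening and hypnotherapeutic session. Table 5 (Process evaluation) lists time under Feasibility and asks whether it was enough for the study procedures, not for the session alone.

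**Coverage.** The same section closes with the statement that "The progression criteria cover components of all of the implementation outcomes". Table 5 lists six outcomes, one of which is Adoption. Its only measure is: "Rate of clinicians consenting to participate among those conducting dressing changes".

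**Recruitment.** The criterion reads "recruitment and study completion rates > 50" (per cent) and names no denominator. The nearest definition is that of Reach, given in Table 5 as "Rate of families willing to participate out of those approached for participation" and in Table 1 (Design) as "Report on the rate of approached eligible families who consent to participate".

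**The concern.** Only children who score medium or high on the suggestibility scale go on to hypnotherapy (Hypnotic suggestibility screening; Intervention phase). A child who consents but whose interview or screening cannot be finished in the time available has no qualifying score and does not commence. That child is a time failure of the intervention as defined, yet is absent from both numerator and denominator.

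The protocol itself expects pressure at this step. Table 2 lists 20 minutes for the scale and 10 for the involuntariness questions, dressing changes usually take 20 to 35 minutes, and the Discussion says that "the duration of the hypnotic suggestibility screening (20 minutes) will make it impractical to conduct hypnotherapy following the screening". The feasibility of screening is among the primary aims and is claimed as a strength of the study. A time criterion that cannot see a failed screening is therefore weak at the step it most needs to judge.

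The coverage sentence matters for a different reason. It assures the reader that every implementation outcome has a bar to clear before an efficacy study, and for clinician consent there is none.

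**Working it through.** **1. Time criterion.** The plan gives a threshold (> 80%) and a denominator, but no expected rate to reproduce. Let s be the number of starters with enough time, 30 the planned number of starters (Sample size), and k the number of consented children who never start for lack of time. The value of k is an assumption; the documents give none.

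- Rule as written: s/30
- Rule with those children counted: s/(30 + k)

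| s | As written | Last k that passes | First k that fails |
|---|---|---|---|
| 30 | 30/30 = 100% | k = 7: 30/37 = 81.1% | k = 8: 30/38 = 78.9% |
| 27 | 27/30 = 90% | k = 3: 27/33 = 81.8% | k = 4: 27/34 = 79.4% |
| 25 | 25/30 = 83.3% | k = 1: 25/31 = 80.6% | k = 2: 25/32 = 78.1% |

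Low scorers are left out of this table. They are excluded by design and are not time failures. At the protocol's 15%, 30 starters imply 30/0.85 = 35.3 screened, so about 5 low scorers. If these count as successes because their screening was completed, the rate is (s + 5)/(35 + k):

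- s = 30: k = 8 gives 35/43 = 81.4% (pass); k = 9 gives 35/44 = 79.5% (fail).
- s = 25: k = 2 gives 30/37 = 81.1% (pass); k = 3 gives 30/38 = 78.9% (fail).

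The tipping point moves by one child in each of these two cases. The conclusion does not change.

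**2. Does the completion criterion catch the same children?** Suppose every such child counts as a non-completer and all 30 starters complete. Then 8 of them give 30/38 = 78.9%, well above 50%. It would take 30 such children, 30/60 = 50%, to fail.

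**3. Coverage.** Matching the listed criteria to the six outcomes in Table 5:

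| Outcome | Criterion |
|---|---|
| Feasibility | sufficient time |
| Acceptability | family satisfaction |
| Reach | recruitment rate |
| Implementation (fidelity) | study completion, data collected, checklist adherence |
| Effectiveness (safety) | no serious side effects |
| Adoption | none |

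**4. Recruitment (secondary).** The Sample size section gives at least 5 potentially eligible children a week for 15 weeks, so 75. Its two 15% losses leave 75 × 0.85 × 0.85 = 54.2 starters, so the stated 30 is reproduced only as a lower bound; the time and coverage points do not depend on it. Working back from 30 starters gives 35.3 consented and screened and 35.3/0.85 = 41.5 approached. The rate is 35.3/41.5 = 85% of those approached but 35.3/75 = 47.1% of the potentially eligible. The second figure is low because it stops at 30 starters, not because families refuse. At the roughly three recruits a week in the Recruitment section it would be 45/75 = 60%. The base can therefore decide which side of 50% the result falls on.

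**The case against.** **The protocol adapts to the time pressure.** The first session is shortened to therapeutic suggestions, Table 2 places screening just before and during the dressing change, and the involuntariness questions follow each test item. Screening need not all fit beforehand. This stands, and it may keep k small. It does not let the criterion see whatever failures remain.

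**Hypnotherapy could be said to commence with the induction inside the scale.** The text makes children eligible for hypnotherapy only after a medium or high score, so this is not the natural reading. It would still drop a child whose interview overran.

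**The criteria are a stated minimum.** This also stands. A reader might infer that the study would automatically proceed despite a failed screening or unwilling clinicians. The documents do not support that: the investigators may weigh other evidence, and Table 5 records time before, during and after the dressing change.

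**Adoption may be covered elsewhere.** Clinicians are participants, and Data synthesis scores every outcome from 1 to 3 using a supplementary file that is not shown. But the Recruitment section speaks of children and parents, Table 5 reports clinician consent separately, and a score is not a progression criterion. The wording about components does not help either, because Adoption has only one.

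**Two stronger readings fail.** A reader might infer that the recruitment criterion is defined on approached families only. It states no base; that one is borrowed from Reach, where both tables use approached families, a valid base for willingness. A reader might also infer that the lack of a screening criterion falsifies the coverage sentence. Screening is a component of the intervention, not a listed implementation outcome, and family satisfaction with it is measured.

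**Conclusion.** Two points hold on the text. First, the time criterion's denominator omits consented children who run out of time before hypnotherapy commences, although interview and screening belong to the intervention. Depending on how the starters fare, between 2 and 8 such children out of 32 to 38 would turn a pass into a fail, or 3 to 9 if about five low scorers count as successes. These counts rest on 30 starters and an assumed k; nothing in the documents predicts how many such children there will be. The completion criterion, at > 50%, is too lenient to stand in for an 80% rule. Second, the coverage sentence is wrong as written, because Adoption has no criterion.

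The recruitment point is smaller: the denominator is unstated, and the choice can matter to the result. Both main points should be corrected before the criteria are applied.

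**What to change.** - **Time.** Make the denominator all consented children who attend their first dressing change. Lack of time for interview, screening or session counts as failure; a low scorer whose screening was completed counts as success. A separate screening-completion criterion is then unnecessary, and one based on children who start screening would again lose those who never reach it.
- **Adoption.** Add a criterion on clinician consent, with a threshold fixed in advance, from the data Table 5 already collects. Alternatively, correct the coverage sentence so that it no longer claims all outcomes.
- **Recruitment.** State the denominator. Report the rate among families approached and, where the clinic log allows, the rate among potentially eligible children presenting while recruitment is open.

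The cost is mainly rewording, plus recording why a consented child did not commence. The eligible-based rate needs more: the Participants section describes children "who agree with their parents to be contacted for research, will be recruited after reviewing their medical files", so it does not show that eligibility is assessed in families who decline contact. The downside is that the reported rates may be less favourable.
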